6.3.5 ARV Treatment Modifications

During the study, all modifications to ARV drugs including subject-initiated and/or protocol-mandated interruptions and permanent discontinuation of treatment will be recorded on the CRFs at each visit. Subject-initiated and protocol-mandated interruptions of study medications include both inadvertent and deliberate interruptions of 1 dose(s), from entry to day 14, 2 doses from days 15 to 56, and >7 cumulative days thereafter.

6.3.6 Clinical Assessments

Complete Physical Exam

A complete physical examination is required at pre-entry and includes an examination of the skin, head, mouth, and neck; auscultation of the chest; cardiac exam; abdominal exam; and examination of the lower extremities for edema*.* The complete physical exam will also include signs and symptoms, diagnoses, vital signs (temperature, pulse, respiration rate*,* and blood pressure), height, and weight.

Targeted Physical Exam

A targeted physical examination is to be driven by any previously identified or new signs or symptoms that the subject has experienced since the last visit. This exam also includes weight, vital signs (temperature, pulse, respiration rate, and blood pressure), and diagnoses.

Signs and Symptoms

All signs, symptoms, deaths, and toxicities must be documented in the subject’s record. At entry,record on the CRFs all signs/symptoms occurring within 42 days prior to entry. After entry record, Grade >3 signs and symptoms on the CRFs.

Any signs or symptoms that lead to a change in study treatment, regardless of grade, must be recorded on the CRFs.

Note: It is only necessary to report the onset date and resolution date on the CRF for any signs or symptoms. For any unresolved signs or symptoms, only changes in grade or resolution need to be reported on the CRF.

Sites must refer to the Division of AIDS Table of Grading the severity of Adult and Pediatric Adverse Events (DAIDS AE Grading Table), Version 1.0, December 2004, which can be found on the DAIDS RCC Web site: http://rcc.tech-res.com/tox_tables.htm.

Diagnoses

Report diagnoses identified by the ACTG criteria for clinical events and other diseases. Refer to the study CRFs for the appropriate appendix used for current ACTG criteria.

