6.3.7 Laboratory Evaluations

Record all protocol-required laboratory values, regardless of grade, obtained at screening, pre-entry and entry on the CRFs. After entry, record all laboratory values Grade >3 on the CRFs. Any laboratory values that lead to a change in study treatment, regardless of grade, will be recorded on the CRFs.

Sites must refer to the Division of AIDS Table of Grading the severity of Adult and Pediatric Adverse Events (DAIDS AE Grading Table), Version 1.0, December 2004, which can be found on the DAIDS RCC Web site: http://rcc.tech-res.com/tox_tables.htm.

Hematology

The following tests are required and performed in real time at the local laboratory: hemoglobin, hematocrit, white blood cell count (WBC), differential WBC, ANC, and platelet count.

Blood Chemistry

The following tests are required and performed in real time at the local laboratory: electrolytes (Na+, K+, Cl-, HCO3), glucose, creatinine, and blood urea nitrogen (BUN).

Calculated Creatinine Clearance

Calculated CrCl is required as estimated by the Cockcroft-Gault equation (refer to section 4.1.4). This requires the recording of all values of serum creatinine regardless of grade.

Liver Function Tests

The following tests are required and performed in real time at the local laboratory: AST (SGOT), lactate dehydrogenase (LDH), ALT (SGPT), and alkaline phosphatase.

Urinalysis

The urinalysis should be completed as per the Schedule of Events and if clinically indicated. Dipstick or microscopic exam may be done. If dipstick results are abnormal, microscopic exam is required.

Pregnancy Testing

All women of reproductive potential (as defined in section 4.1.5) must have a negative serum or urine beta-human chorionic gonadotropin (-HCG) pregnancy test result at screening and within 48 hours prior to initiating protocol-specified medications and any time thereafter that pregnancy is suspected. (The urine test must have a sensitivity of 25-50 mIU/mL).

Hepatitis B Serology

Documentation of hepatitis B infection status by hepatitis B surface antigen is required prior to study entry. Previous results verifiable by reports from a CLIA-certified laboratory are acceptable any time prior to study entry.

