9.2.2.4 Safety and Tolerability

- Incidence of Grade 3 and 4 symptoms and laboratory results by body system and by type, excluding asymptomatic elevations in lipids or CK.
- Incidence of permanent discontinuation of study medication for any reason.
- Incidence of permanent discontinuation of study medication for reasons other than virologic failure.
  - - 1. Change in CD4+ T-cell count from baseline to weeks 24, 48, and 72. The baseline CD4+T-cell count will be the arithmetic mean of the two measurements obtained on different days closest before or on the day of study medication dispensation (e.g., pre-entry and entry determinations). If only one such measurement is available, then this measurement will be the baseline value.
      2. RAL-, FTC- and TDF-resistance mutations using very sensitive resistance assay measures in subjects with detectable viremia.
      3. Subject-specific estimates of: (a) the minimum concentration (Cmin) for RAL, FTC, and TDF; (b) viral load changes on day 7; (c) CD4+ T-cell counts changes over days 0-14 (magnitude of changes and estimated slope). The baseline HIV-1 RNA will be the geometric mean of the two measurements obtained on different days closest before or on the day of study medication dispensation (e.g., pre-entry and entry determinations). If only one such measurement is available, then this measurement will be the baseline value.
      4. Adherence by self-report at each study visit.
      5. Total cell-associated proviral DNA, LTR circular DNA, and integrated proviral DNA as measured by an assay currently undergoing validation; and unintegrated linear proviral DNA calculated by subtraction, measured on days 0, 2, 7, 10, 14, 21, 28, and 56; weeks 12, 24, 48, and 72; and at the time of virologic failure.
      6. Plasma HIV-1 RNA levels collected from week 24 through week 72, as quantified by the single copy assay. If enough points are above the lower limit of the single-copy assay, the rate of change over the third (and possibly fourth) phase of viral decay will be estimated.
      7. CD4+ T-cell counts measured on days 0, 2, 7, 10, and 14.

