## 9.5 Monitoring

As phase I/II and pilot studies are not routinely reviewed by the Data and Safety Monitoring Board, it is the responsibility of the Team Safety Monitoring Committee (TSMC) to interpret toxicity data and make any decisions needed to protect subjects from undue risk. The TSMC will convene once a month to review monitoring reports. At a minimum the TSMC will consist of the protocol chair, the protocol vice chair, the DAIDS medical officer, the statisticians, the data manager, and the Network Community Advisory Board representative to the team.

In addition, toxicity summaries will be reviewed annually by the Study Monitoring Committee of the Translational Research and Drug Development (TRADD).

The safety and tolerability of the study medication will be monitored by means of adverse event reports (AER) and toxicity summaries presenting counts of subjects by Grade ≥ 3 laboratory and clinical events. It is required that these data be entered into the database within 3 business days of the time at which the results of the laboratory tests or clinical examinations become available. Toxicity summaries will be reviewed monthly via conference calls or by e-mail exchange. Subjects will be managed according to Section 7.0.

The data manager and statistician will also provide accrual reports (number of subjects accrued, number and percent discontinuing for any reason) and reports that identify subjects who meet the criterion for virologic failure. To facilitate sites in providing clarifications, SIDs will not be masked.

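### The post-entry CRF recording threshold (Grade >3) contradicts the Grade 3 and 4 safety endpoint and the Grade ≥3 monitoring rule, so Grade 3 events that leave treatment unchanged could go unrecorded

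*Protocol*

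**What the plan says.** Two sections of the protocol govern what goes on the CRF after entry. For symptoms, 6.3.6 says: "After entry record, Grade >3 signs and symptoms on the CRFs". For laboratory results, 6.3.7 says: "After entry, record all laboratory values Grade >3 on the CRFs".

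Both sections widen the rule where treatment is altered: "Any signs or symptoms that lead to a change in study treatment, regardless of grade, must be recorded on the CRFs" (6.3.6) and "Any laboratory values that lead to a change in study treatment, regardless of grade, will be recorded on the CRFs" (6.3.7). For creatinine, 6.3.7 goes further: "This requires the recording of all values of serum creatinine regardless of grade".

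Two other sections use the recorded data:

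- The first component of the safety endpoint in 9.2.2.4 is "Incidence of Grade 3 and 4 symptoms and laboratory results by body system and by type, excluding asymptomatic elevations in lipids or CK". Under 9.6.2.4 it is analysed as the proportion of treated subjects in each event category, with an exact binomial 95% CI, and as incidence rates per person-months.
- Section 9.5 monitors safety through adverse event reports and "toxicity summaries presenting counts of subjects by Grade ≥ 3 laboratory and clinical events". It requires the data in the database within 3 business days of the result becoming available, and has the summaries reviewed monthly.

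**The concern.** The sections that collect the data and the sections that use them set different grade thresholds. Grade >3 means Grade 4 and above, while the endpoint and the monitoring rule both start at Grade 3. A site cannot meet 9.5 by doing only what 6.3.6 and 6.3.7 ask.

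A later analysis plan cannot repair this, because it can analyse only what was recorded. The Grade 3 events that did reach the CRF would mostly be those that altered treatment. Capture would then depend on how the investigator judged causality and managed the event, whereas the endpoint is defined by grade alone. The result would be a selective undercount, affecting secondary objective 1.3.4 and the summaries that the Team Safety Monitoring Committee reviews.

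**Working it through.** The protocol states no figure to reproduce here and gives no Grade 3 event rate. The check therefore sets the thresholds side by side and traces which events pass through.

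**Step 1: thresholds**

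| Protocol section | Purpose | Threshold |
| --- | --- | --- |
| 6.3.6 | CRF recording of symptoms after entry | Grade >3 |
| 6.3.7 | CRF recording of laboratory values after entry | Grade >3 |
| 9.2.2.4 | Safety endpoint | Grades 3 and 4 |
| 9.5 | Monthly toxicity summaries, with timed database entry | Grade ≥3 |

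**Step 2: what the literal CRF rule captures**

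- Grade 4 symptoms and laboratory values: recorded.
- Grade 3 events that change study treatment: recorded, through the treatment-change rule. Section 7.2 generally has the regimen stopped for Grade 3 events possibly related to RAL, so many related events come in this way.
- Creatinine: recorded at every grade.
- Grade 3 symptoms and other laboratory values with treatment unchanged: not recorded under 6.3.6 or 6.3.7, although 9.2.2.4 counts them and 9.5 requires them.

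**Step 3: does the last group exist under this protocol?** It does, because the toxicity section provides for it:

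- Section 7.2 allows dosing to continue when there is compelling evidence that RAL did not cause a Grade 3 event.
- Section 7.7.1 allows the regimen to continue through asymptomatic, isolated AST or ALT elevations up to Grade 3.
- Section 7.5 provides for antiemetics, with the regimen held for Grade 3 or worse nausea and vomiting that these do not improve. An episode that responds need not change treatment.

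The endpoint in 9.2.2.4 is restricted neither to related events nor to those that alter treatment, so all three kinds belong in it.

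**Step 4: direction and scale.** For a given category, let *a* be the number of subjects with a Grade 4 event or a Grade 3 event that is captured. Let *u* be the number whose only qualifying events are Grade 3 with treatment unchanged. With *N* treated subjects:

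- proportion as defined in 9.2.2.4: (*a* + *u*)/*N*
- proportion from literal recording: *a*/*N*
- shortfall: *u*/*N*, which is never negative

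The error therefore goes only towards undercounting. For scale, assume that all 34 planned subjects are treated and no replacements are added. Each such subject then lowers the reported proportion by 1/34 = 0.029, or about 3 percentage points. The value of *u* cannot be obtained from the documents, so neither can the total shortfall.

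**The case against.** The strongest objection is that everything turns on one symbol in text extracted from a file in which symbols have visibly been damaged. The laboratory limits in 4.1.4, the age limit in 4.1.7 and the dose counts in 6.3.5 have lost their comparison signs, and a Greek letter is missing in 6.3.7 itself. An underlined > meant as ≥ could have been read as a plain >. This cannot be excluded. Against it, the comparison signs evidently lost elsewhere disappeared and did not turn into a different sign. The ≥ sign prints correctly in sections 7.2 to 7.7 and in 9.5, and the same >3 appears in two separate sections. As the text stands, the contradiction is there.

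Second, section 11.2.1 says that the data management center will provide the CRF recording instructions, and these are not shown. They may already use Grade ≥3. That is a reason to check them, but it does not make the protocol consistent.

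Third, a reader might infer that Grade 3 events would be absent from the database altogether, that the safety objective could not be computed, or that monthly review would miss most Grade 3 signals without any oversight beyond the study team. The documents do not support these stronger readings:

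- Any-grade events that change treatment, and all creatinine values, are recorded.
- Section 9.5 itself demands entry of Grade ≥3 data, so a site faces two conflicting instructions, not a single instruction to omit.
- Section 11.4 requires expedited reporting of serious adverse events and of all cancers.
- Section 6.3.6 requires every sign, symptom and toxicity to be documented in the subject's record, so omitted events can be recovered.
- The two components of 9.2.2.4 on permanent discontinuation are untouched.
- Section 9.5 places the DAIDS medical officer on the monitoring committee and adds an annual toxicity review by a network committee.
- No event rate is given to support a claim about most Grade 3 signals.

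**Conclusion.** The point holds as an internal contradiction. Sections 6.3.6 and 6.3.7 set a CRF threshold that excludes Grade 3, while 9.2.2.4 and 9.5 require Grade 3. The exposure is confined to Grade 3 symptoms and non-creatinine laboratory values that leave study treatment unchanged. If sites follow the recording sections literally, one component of a secondary safety endpoint and the monthly toxicity summaries are undercounted, in a way that depends on causality judgement and management.

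This rests on two assumptions: that the source file does read >3, and that the CRF instructions do not already apply ≥3. Nothing in the documents shows that any event has in fact been omitted. The estimate of d1 and the sample size are unaffected. The correction should be made because it is almost free and both a stated objective and safety monitoring use these data.

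**What to change.** 1. Check the source file of the protocol. If 6.3.6 and 6.3.7 read ≥3 there, nothing in the protocol needs changing.
2. If they read >3, change both sentences to Grade ≥3, so that recording agrees with 9.2.2.4 and 9.5. Keep the existing rules on treatment changes and creatinine.
3. Confirm that the CRF instructions from the data management center use the same threshold, and tell sites of the correction.
4. If Grade 3 events are found to have been left off the CRF, enter them from source records.

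The cost is one symbol in each of two sentences, a note to sites and a small amount of extra data entry. The change concerns data capture only and alters no rule on treatment or toxicity management.

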6.3.7 Laboratory Evaluations

Record all protocol-required laboratory values, regardless of grade, obtained at screening, pre-entry and entry on the CRFs. After entry, record all laboratory values Grade >3 on the CRFs. Any laboratory values that lead to a change in study treatment, regardless of grade, will be recorded on the CRFs.

Sites must refer to the Division of AIDS Table of Grading the severity of Adult and Pediatric Adverse Events (DAIDS AE Grading Table), Version 1.0, December 2004, which can be found on the DAIDS RCC Web site: http://rcc.tech-res.com/tox_tables.htm.

Hematology

The following tests are required and performed in real time at the local laboratory: hemoglobin, hematocrit, white blood cell count (WBC), differential WBC, ANC, and platelet count.

Blood Chemistry

The following tests are required and performed in real time at the local laboratory: electrolytes (Na+, K+, Cl-, HCO3), glucose, creatinine, and blood urea nitrogen (BUN).

Calculated Creatinine Clearance

Calculated CrCl is required as estimated by the Cockcroft-Gault equation (refer to section 4.1.4). This requires the recording of all values of serum creatinine regardless of grade.

Liver Function Tests

The following tests are required and performed in real time at the local laboratory: AST (SGOT), lactate dehydrogenase (LDH), ALT (SGPT), and alkaline phosphatase.

Urinalysis

The urinalysis should be completed as per the Schedule of Events and if clinically indicated. Dipstick or microscopic exam may be done. If dipstick results are abnormal, microscopic exam is required.

Pregnancy Testing

All women of reproductive potential (as defined in section 4.1.5) must have a negative serum or urine beta-human chorionic gonadotropin (-HCG) pregnancy test result at screening and within 48 hours prior to initiating protocol-specified medications and any time thereafter that pregnancy is suspected. (The urine test must have a sensitivity of 25-50 mIU/mL).

Hepatitis B Serology

Documentation of hepatitis B infection status by hepatitis B surface antigen is required prior to study entry. Previous results verifiable by reports from a CLIA-certified laboratory are acceptable any time prior to study entry.

6.3.8 Immunologic Studies

CD4+/CD8+

CD4+/CD8+ T-cell counts and percentages will be obtained as per the Schedule of Events. Pre-entry and entry measurements must be obtained at two separate time points at least 48 hours apart and no more than 14 days apart. The mean of the pre-entry and entry measurements will be used as the baseline value.

Evaluations for CD4+ and CD8+ T-cell counts and percentages should be performed at the same laboratory, if possible, for baseline calculation and throughout the course of the study. The laboratory performing the CD4+ and CD8+ T-cell evaluations must have CLIA certification, or its equivalent. The laboratory also must participate in and be certified for protocol testing by the DAIDS Immunology Quality Assurance (IQA) Program.

Because of the diurnal variation in CD4+ and CD8+ T-cell counts, determinations for individual subjects should be obtained consistently in either the morning or the afternoon throughout the study.

CD4+ and CD8+ T-cell counts (absolute and percentage) must be recorded in the source document and on the CRFs.

Advanced Flow Assay

Blood will be collected and PBMCs cryopreserved for advanced flow testing. Refer to Appendix II for details concerning processing and shipping of the specimens.

Specific lymphocyte marker testing includes the following:

- Proportions of Ki-67+ cells of CM T-cells at baseline.
- Proportion of CD45RA-/CD27+ cells (CD4+ or CD8+ ) that: (a) are in cell cycle (Ki-67+) and/or (b) express one or both activation markers CD38, HLA-DR, as measured at baseline.
- Proportions of activated CM (CD45RA-CD27+) CD4+ and CD8+ T-cells between baseline and inflection point.
- Proportion of phenotypically defined naïve (CD45RA+/CD27+), CM (CD45RA-/CD27+) and effector memory (CD45RA-/CD27-) CD4+ and CD8+ T-cells that are in cell cycle (Ki-67+) or express the activation markers CD38 and HLA-DR.

NOTE: The advanced flow assay also requires CD4+/CD8+ and WBC with differential from a sample obtained at the same time.

Plasma Bacterial 16s DNA

Bacterial 16s DNA levels will be obtained as per the Schedule of Events. Refer to Appendix II for details concerning processing and shipping of the specimens.

6.3.9 Virologic Studies

Plasma HIV-1 RNA (real-time and batched)

Screening plasma HIV-1 RNA level should be obtained within 42 days prior to study entry by any FDA-approved test for quantifying HIV-1 RNA. Any plasma HIV-1 RNA value performed locally in a CLIA-certified laboratory within 42 days prior to study entry can be used as the screening value.

Plasma HIV-1 RNA samples obtained at entry through day 21 should be batched and shipped according to Appendix II. Plasma HIV-1 RNA for all other study time points will be tested in real time and shipped according to Appendix II.

Eligibility will be determined based on the screening HIV-1 RNA value. The baseline value will be the geometric mean of the pre-entry and entry determinations, which must have been obtained at least 48 hours after pre-entry, but no more than 14 days apart. Plasma HIV-1 RNA quantification after screening will be measured by Johns Hopkins University Virology Specialty Laboratory using the current approved UltraSensitive Roche Amplicor HIV-1 Monitor assay.

HIV-1 RNA Single Copy Assay (batched)

Plasma HIV-1 RNA will also be measured using the single copy assay for HIV-1 RNA samples with <50 copies/mL.  Samples will be collected as per the Schedule of Events and processed and shipped as per Appendix II. The single copy assays will be done as batched tests, not in real time.

Proviral DNA, LTR Circular DNA, Integrated Proviral DNA

Total cell-associated proviral DNA, LTR circular DNA, and integrated proviral DNA will be measured from PBMCs. Samples will be collected as per the Schedule of Events and processed and shipped as per Appendix II.

Genotype

Genotypic resistance testing is required prior to study entry. For the screening genotype, previous results verifiable by reports from a local CLIA-certified laboratory are acceptable any time prior to study entry as long as the results are available at entry. Genotype results should be part of the source documentation.

NOTE: A plasma sample for genotypic resistance testing should be obtained and stored at pre-entry for subsequent use as a baseline.

At or after week 16 when a subject is suspected to have virologic failure, a confirmatory plasma HIV-1 RNA and a plasma sample for real-time genotyping will be collected. The specimen collected for genotyping at that visit will be sent as per the instructions in Appendix II for resistance testing once virologic failure has been confirmed. Real-time results will be shared with sites.

Stored Plasma and Stored PBMCs

Plasma and PBMCs will be stored at the ACTG repository for future virologic assays. Refer to Appendix II regarding shipping instructions for the stored plasma and stored PBMCs.

NOTE: Stored plasma and stored PBMC samples should not be obtained if a subject is off study treatment, i.e., subject has permanently discontinued all study medications.

